**Specific Objectives**

1. To develop, validate, implement intervention, and evaluate the effectiveness of a health educational intervention in improving knowledge of breast cancer, knowledge, beliefs, and practices of breast self-examination.
2. To determine a significant association between the respondent’s characteristics, knowledge of breast cancer, knowledge, beliefs, and practices on breast self-examination among college teachers.
3. To determine the differences between and within the control, and intervention group, pre and post intervention on knowledge of breast cancer, knowledge, beliefs, and practice of breast self-examination at baseline, 1 month, and 3 months post interventions.

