**Study Design:**

A single blinded, cluster randomized controlled trial (cRCT) will be carried out among female college teachers from government colleges in Hyderabad district. Colleges will serve as randomization units (clusters). The study will proceed through three phases:

**Baseline Data Collection:** Data will be collected from both control and intervention groups.

**Intervention Delivery**: The intervention will be administered to the intervention group during this phase.

**Follow-up Data Collection**: Follow-up data will be collected at two different post-intervention points: one month and three months later. The same questionnaire will be used for both control and intervention groups. The intervention module will be applied to the control group after the study's completion.

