**Step 4: Proportionate Stratified sampling:**

Proportionate stratified sampling from all colleges based on faculty will be performed once the assignment of colleges is done to the intervention and control group, e.g., 2 colleges in the intervention group.

To calculate the proportions for each faculty within the intervention group (57) for the two colleges (A & B), these steps can be followed.

Proportions will be calculated based on the number of teachers in each faculty at each college.

e.g.

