## 2.8 Study outcomes

**2.8.1 Primary outcome**

The primary outcome for this study is the practice of Breast Self-Examination (BSE). This will be assessed based on the percentage of participants who consistently and effectively perform breast self-examinations. Participants will self-report on their BSE practices using a structured questionnaire. Regular BSE practice will be defined as performing the examination once a month, while any other response indicating irregular BSE will be categorized as non-practicing.

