## Data Summarizing and Analysis

The statistical analysis for this study will be conducted using IBM SPSS Statistics software, version 26.0. Before performing any statistical tests, continuous variables will be evaluated for their distribution characteristics. Variables that display a normal distribution will be summarized using descriptive statistics such as mean and standard deviation. In contrast, continuous variables that do not follow a normal distribution will be described using the median and interquartile range (IQR).

For categorical or dichotomous data, descriptive statistics will include percentages, counts, or proportions to effectively summarize the data. Statistical comparisons between categorical data from the intervention and control groups will be conducted using Chi-square tests or Fisher's exact tests, as appropriate. Differences in means of normally distributed continuous variables between these groups will be assessed using independent-samples t-tests. Meanwhile, non-normally distributed continuous data will be compared using the Mann-Whitney U test.

Given the clustered nature of the study design, Generalized Estimating Equations (GEE) will be employed for statistical analysis. GEE is robust for analyzing data that exhibit correlation within clusters (e.g., colleges and teachers within colleges). It will enable the assessment of group effects (intervention vs. control), time effects (pre- vs. post-intervention), and their interaction effect (group*time) over the study period.

We will analyze all the data collected from both the intervention and control groups, even if participants drop out. This approach is called Intention-to-Treat (ITT). If someone stops participating before the study ends, we will use their last recorded information to fill in any missing data. This method helps ensure that our results are accurate and unbiased, even when people leave the study early.

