### Appendix II. Sample size calculations

Phase II(CRCT)

To determine a significant association between the respondent’s characteristics, knowledge, beliefs, and practices on breast self-examination among college teachers.

Sample size calculation will be done by applying formula two proportion/two sample for t testing hypothesis and observing expected differences in proportions of BSE practice between two groups.

n = [(Z_ı - α)√(2P̅(1 - P̅)) + (Z_ı - β)√(Pı(1 - Pı) + P2(1 - P2))] / (Pı - P2)²

Table 3.3: Information of sample size derivation

| **Attribute** | **Assumptions** |
| --- | --- |
| **Z** | Cluster Randomized Controlled Trial |
| **Z(1-α)** | Zα= 1.96; p-value= 0.05; therefore, power desired is 0.95 |
| **Z(1−β)** | Zβ=0.84; β=0.20; 0.80 power was desired. (James 2001) |
| **P1** | P1=85.6% Prevalence of regular breast self-examination practice in intervention group 06 months post intervention(ABDULRAHMAN, 2020) |
| **P2** | P2=26%, Prevalence of regular breast self-examination practice in control group 06 months post intervention(ABDULRAHMAN, 2020) |

Sample size n= **14** calculated by openEpi(Charan & Biswas, 2013) 2 groups 14* 2 = 28

28 x [1 + (m-1) ICC)

Where: m=average cluster size,

ICC-class correlation coefficient m

ICC =0.02: intra-cluster correlation coefficient based on Cluster randomised controlled trial comparing the effectiveness and cost-effectiveness of two primary care interventions aimed at improving attendance for breast screening (Richards et al., 2001),

m= 99 (average cluster size calculated)

n​=28×[1+(m−1) ×ICC]

Given that average cluster size =99

ICC=0.02:

n=28× [1+(99−1) ×0.02]

n=28× [1+98×0.02]

n=28× [1+1.96]

n=28×2.96

n≈82.88

Rounding up to the nearest whole number, the final adjusted sample size without considering attrition and eligibility adjustments would be approximately 83.

To adjust for a 20% attrition rate, we need to increase the sample size by dividing it by the complement of the attrition rate, which is 1-0.2 = 0.8. So:

83 / 0.8 = 103

To adjust for the eligibility proportion of 90%, we need to further increase the sample size by dividing it by the eligibility proportion. So:

103 / 0.9 = 114

The final required sample size with attrition and eligibility adjustments is approximately 114 teachers.

114/2 =57

57 participants in each group.

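### No primary contrast is named and no baseline value is adjusted for; the only treatment-by-time term is a change-from-baseline contrast, usually less precise than a baseline-adjusted 3-month comparison

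*Combined protocol and SAP*

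**What the plan says.** All references are to the combined protocol and SAP.

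- **Model.** Data Summarizing and Analysis plans a GEE for group effects, "time effects (pre- vs. post-intervention), and their interaction effect (group*time) over the study period". No covariate is listed.
- **Other tests.** The same section also plans simple comparisons: "Statistical comparisons between categorical data from the intervention and control groups will be conducted using Chi-square tests or Fisher's exact tests, as appropriate", with t-tests or Mann-Whitney tests for continuous variables. It does not say which of these analyses, or which visit, gives the primary treatment effect.
- **Data available.** Under Study Design, the baseline phase states: "Data will be collected from both control and intervention groups". After that, "Follow-up data will be collected at two different post-intervention points: one month and three months later". Section 2.14 says that the follow-up questionnaire repeats the baseline one except for its first section, so practice, knowledge and beliefs are measured in the same way at all three visits.
- **Primary outcome.** Section 2.8.1 makes it binary: "Regular BSE practice will be defined as performing the examination once a month", with anything else counted as not practising.
- **Sample size.** Appendix II compares two follow-up proportions, 85.6% and 26%, with "Zα= 1.96; p-value= 0.05" and 80% power. Baseline plays no part in it.

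**The concern.** There are two linked gaps.

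First, the plan offers several candidate answers to its main question: a group term, a group*time term (more than one coefficient if the three visits are kept separate) and a plain two-group test at either follow-up. Nothing fixes which one counts. A group term averaged over all visits would also include baseline, when no effect can exist yet.

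Second, none of these candidates is a follow-up comparison adjusted for baseline. The group*time term does use baseline, but by subtracting it, which carries the noise of both measurements into the estimate. If a teacher's baseline practice only weakly predicts her later practice, subtraction can be less precise than ignoring baseline. With four colleges and 114 teachers, there is little precision to spare.

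**Working it through.** **1. The plan's own figure.** For 85.6% against 26%, two-sided 0.05 and 80% power, the two-proportion formula gives 10 per group, or 13 with continuity correction; the plan has 14. Then 28 × (1 + 98 × 0.02) = 82.88, rounded to 83. Next, 83/0.8 = 103.75 and 103.75/0.9 = 115.3. The plan truncates to 103 and gets 103/0.9 = 114.4, hence 114. The figure reproduces within rounding, and it rests on a follow-up comparison, not on a change contrast.

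**2. Textbook comparison.** Set the variance of a follow-up-only comparison to 1 and let r be the baseline-to-follow-up correlation. With equal variances and independent teachers, the change contrast has variance 2(1 − r) and the adjusted comparison 1 − r². At r = 0.3 these are 1.40 and 0.91; at r = 0.5 they are 1.00 and 0.75. The documents give no r, and this formula ignores colleges.

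**3. At college level.** The plan supplies an ICC of 0.02 and two colleges per arm. Completers per college are 57 × 0.8 / 2 = 22.8, taken as m = 23. Two inputs are assumed: teacher-level r = 0.3 and correlation c of the college effect over time, from 0.8 to 1.0. For a college mean:

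- variance V = ICC + (1 − ICC)/m = 0.02 + 0.0426 = 0.0626
- covariance over time C = ICC × c + r(1 − ICC)/m
- change contrast: 2(V − C)
- teacher-level adjustment with slope b = ICC × c + (1 − ICC)r: V(1 + b²) − 2bC

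| ICC | c | C | b | Change | Adjusted | Variance cut |
|---|---|---|---|---|---|---|
| 0.02 | 0.8 | 0.0288 | 0.310 | 0.0677 | 0.0508 | 25% |
| 0.02 | 1.0 | 0.0328 | 0.314 | 0.0597 | 0.0482 | 19% |
| 0.05 (assumed) | 0.8 | 0.0524 | 0.325 | 0.0778 | 0.0669 | 14% |
| 0.05 (assumed) | 1.0 | 0.0624 | 0.335 | 0.0578 | 0.0597 | −3% |
| 0.10 (assumed) | 0.9 | 0.1017 | 0.360 | 0.0748 | 0.0839 | −12% |

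At the plan's ICC, the change contrast has 1.08 (c = 0.8) to 0.95 (c = 1.0) times the variance of ignoring baseline altogether. The adjusted comparison has 0.81 to 0.77 times that variance.

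**4. Is a low r plausible?** Assume 26% regular BSE at baseline, equal to the planned control rate. In the intervention arm at the planned 85.6%, two binary variables with these margins cannot correlate above √[(0.26 × 0.144)/(0.74 × 0.856)] = 0.24. At a 10% baseline the ceiling is 0.14. A large planned effect therefore forces a low correlation in that arm.

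Give that arm its maximum correlation (covariance 0.0374) and assume r = 0.5 in controls (covariance 0.0962). The outcome variances are 0.856 × 0.144 = 0.1233 and 0.26 × 0.74 = 0.1924. On the risk-difference scale, ignoring clustering and before dividing by the number per arm:

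- follow-up only: 0.1233 + 0.1924 = 0.3157
- change: (0.1233 + 0.1924 − 2 × 0.0374) + 2 × 0.1924 × 0.5 = 0.433
- adjusted, common slope: 0.3157 − (0.0374 + 0.0962)²/(2 × 0.1924) = 0.269

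Here the change contrast has 0.433/0.3157 = 1.37 times the variance of ignoring baseline.

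**5. Degrees of freedom.** Four colleges in two arms leave 2 df (t critical value 4.30). Adjusting for a college-mean baseline leaves 1 df (12.7). Adjusting for each teacher's own value keeps 2 df.

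**The case against.** The strongest reply is that group*time is a valid contrast and answers the third specific objective, "To determine the differences between and within the control, and intervention group, pre and post intervention". It also removes stable college differences completely, whereas teacher-level adjustment removes them only in part. With four colleges that matters: the last two rows of the table show adjustment losing slightly or clearly. Allocation adds to this. Under section 2.7, whole blocks of two colleges are assigned together and teachers are sampled afterwards. Section 2.11 withholds the purpose of the intervention from control colleges at recruitment. Real baseline differences between arms are plausible, and the two analyses could then differ in the estimate as well as in precision. All of this stands. It is why the change contrast should be kept as a sensitivity analysis.

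Several stronger readings are tempting but are not supported:

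- **That the plan takes its effect from group*time.** It does not say so. It lists three GEE terms and separate two-group tests without choosing.
- **That adjustment saves 20% to 40% of the variance.** This is (1 + r)/2 for r from 0.6 down to 0.2, a result for individually randomised, equal-variance data. Here colleges are randomised and the outcome is binary.
- **That adjustment costs nothing.** It can lose precision when college effects are large and stable, a college-mean covariate would cost a degree of freedom, and a baseline-adjusted odds ratio is conditional rather than marginal.
- **That forcing a common baseline mean is an equivalent route.** The allocation and recruitment just described make that assumption doubtful.
- **That faculty should be a covariate.** The plan says "Proportionate stratified sampling from all colleges based on faculty will be performed", but nothing in it shows that faculty predicts BSE practice.

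**Conclusion.** The point holds in this form: the plan names no primary contrast or time point, adjusts for no baseline value, and has as its only treatment-by-time term a change contrast that does not correspond to the sample-size basis. This is a loss of precision and a gap in specification. It is not an invalid analysis.

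The size is moderate. At the plan's ICC, teacher-level adjustment cuts the variance of the change contrast by about 19% to 25%, assuming teacher-level r = 0.3 and a college-effect correlation of 0.8 to 1.0. The cut is 14% at an ICC of 0.05 with c = 0.8, and there is none at c = 1.0. The documents give neither correlation. If baseline practice is near 26%, their planned rates do hold r in the intervention arm at or below about 0.24, so the change contrast is likely to be inefficient for the primary outcome.

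**What to change.** Before follow-up data are examined by arm, amend Data Summarizing and Analysis to state:

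- **Primary estimate.** The intervention-minus-control difference in the proportion practising regular monthly BSE at 3 months, from a model adjusted for each teacher's own baseline BSE practice, standardised to a marginal risk difference, with college as the clustering unit. The covariate is the teacher's value, not the college mean.
- **Secondary outcomes.** The same form for knowledge and belief scores, with the baseline score as covariate. One month is a secondary time point.
- **Sensitivity analysis.** The group*time change contrast, with a note that it may differ from the primary estimate if the colleges differ at baseline.
- **Simple two-group tests.** Label these descriptive.

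Inference suited to four clusters is needed whichever contrast is chosen and is a separate matter.

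The cost is a few sentences, with no extra data and no design change. The drawback is small: teacher-level adjustment leaves part of any stable college difference in the estimate, which the sensitivity analysis would help to reveal.

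### Carrying the last value forward is the only missing-data rule; it is unbiased only if practice stops changing at dropout, and the error can go either way

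*Combined protocol and SAP*

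**What the plan says.** The Data Summarizing and Analysis section commits to intention-to-treat and then gives one rule for dropouts: "If someone stops participating before the study ends, we will use their last recorded information to fill in any missing data". It adds: "This method helps ensure that our results are accurate and unbiased, even when people leave the study early". No missing-data assumption, other method or sensitivity analysis appears there or elsewhere.

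The rule feeds a GEE model, of which the section says: "It will enable the assessment of group effects (intervention vs. control), time effects (pre- vs. post-intervention), and their interaction effect (group*time) over the study period". The primary outcome in section 2.8.1 is binary: "Regular BSE practice will be defined as performing the examination once a month". On timing, the Study Design text says: "Follow-up data will be collected at two different post-intervention points: one month and three months later". Appendix II expects substantial loss: "To adjust for a 20% attrition rate, we need to increase the sample size by dividing it by the complement of the attrition rate".

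**The concern.** LOCF gives the right average only if the carried value matches, on average, what the missing questionnaire would have shown. This trial is built to break that condition. A teacher lost before month 1 has her pre-intervention answer entered as her month-1 and month-3 outcome. A teacher lost after month 1 is recorded as unchanged to month 3. In both cases later change is set to exactly zero, and change by arm is what the group-by-time term and the third specific objective are meant to measure.

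Intention-to-treat does not require this. It fixes the arm in which each teacher is analysed, not how missing answers are filled. At stake are the estimate of the primary effect, its interval, and an assurance about bias that the plan does not support.

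**Working it through.** **The plan's own figure.** Appendix II starts from 14 per arm. Its two-proportion formula with 85.6% and 26% gives 9.63, rounded up to 10. A continuity correction then gives 13.14, so 14. Next, 28 × (1 + 98 × 0.02) = 82.88, so 83; 83/0.8 = 103.75 (written as 103); 103/0.9 = 114.4, so 114, or 57 per arm. The figure reproduces to rounding (rounding up at each step gives 116). It is already inflated for 20% attrition, which is about 0.2 × 57 = 11 teachers per arm.

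**Inputs from the documents.** Attrition is 20%. The intervention rate is given as "P1=85.6% Prevalence of regular breast self-examination practice in intervention group 06 months post intervention", and the control rate at the same time is 26%.

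**Assumptions, not in the documents.** The six-month rates hold at month 3; month 3 is the outcome visit (section 2.8.1 names none); baseline B is equal in both arms (5% to 26% tried); control practice is at its final level by month 1; dropout is unrelated to practice. Dropout timing, unequal dropout and waning are scenarios only.

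**Formula.** With shares d0 lost before month 1 and d1 lost after it, and rates B, M1 and M3 at the three visits:

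filled month-3 rate = (1 − d0 − d1) × M3 + d0 × B + d1 × M1

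Results in percentage points, with 20% lost per arm unless stated and B = 26:

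| Scenario | Intervention | Control | Difference | True | Bias |
|---|---|---|---|---|---|
| (a) all before month 1 | 0.8×85.6 + 0.2×26 = 73.7 | 26.0 | 47.7 | 59.6 | −11.9 |
| (b) half before, half after, stable from month 1 | 0.8×85.6 + 0.1×26 + 0.1×85.6 = 79.6 | 26.0 | 53.6 | 59.6 | −6.0 |
| (c) all after, stable | 85.6 | 26.0 | 59.6 | 59.6 | 0 |
| (d) all after, waning 85.6 to 60 | 0.8×60 + 0.2×85.6 = 65.1 | 26.0 | 39.1 | 34.0 | +5.1 |
| (e) before month 1, 30% vs 10% lost | 0.7×85.6 + 0.3×26 = 67.7 | 26.0 | 41.7 | 59.6 | −17.9 |
| (f) no effect, both arms 26 to 50, 30% vs 10% lost before month 1 | 0.7×50 + 0.3×26 = 42.8 | 0.9×50 + 0.1×26 = 47.6 | −4.8 | 0 | −4.8 |

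In (a) and (b) the baseline cancels between arms: 0.8 × 59.6 = 47.7 and 0.9 × 59.6 = 53.6 for any equal B. In (e) it does not; B = 5 gives a bias of −22.1.

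**How many filled values are wrong.** The outcome is binary, so a carried value is wrong only if that teacher's status changed. In (a), between 85.6 − 26 = 59.6% and 74 + 14.4 = 88.4% of intervention teachers change status, depending on within-person correlation. Wrong values are then 0.2 × 59.6 = 11.9% to 0.2 × 88.4 = 17.7% of the arm.

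**Uncertainty.** In 20,000 simulated trials (57 per arm, latent correlation 0.5, random dropout, no clustering), the standard error of the change-from-baseline contrast was 0.091 under LOCF against 0.107 from observed records in (a), 0.094 against 0.107 in (b), and 0.100 against 0.112 in (d). Nominal 95% intervals covered the true value 74%, 90% and 92% of the time; observed-record intervals covered about 95%.

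For a plain month-3 comparison in (a), LOCF gives √(0.737×0.263/57 + 0.26×0.74/57) = 0.082. Observed records (0.8 × 57 = 45.6 per arm) give √(0.856×0.144/45.6 + 0.26×0.74/45.6) = 0.083, almost the same. With baseline and control both at 10%, the simulated LOCF standard error was the larger (0.072 against 0.067).

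**The case against.** Several points on the other side stand.

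- A reader might infer that a fifth of month-3 outcomes would be wrong. They would not: in the worst equal-dropout case the share is 11.9% to 17.7% of the intervention arm.
- A reader might infer that LOCF always understates uncertainty. It does not. The standard error was smaller for the group-by-time contrast in every scenario run, but not for every month-3 comparison. The lost coverage comes mainly from bias: the interval is narrow and centred in the wrong place.
- A reader might infer that practice peaks at month 1 and then fades, so that LOCF flatters the intervention. Nothing in the documents shows this. Section 2.12 runs reminders for three months, and the planning rate of 85.6% is itself a six-month figure. Scenario (d) shows what waning would do, not what is expected.
- Scenario (a) needs every dropout to leave before month 1. With stable practice and only later losses the bias is zero.
- On the planning rates, equal dropout shrinks the effect without reversing it: 47.7 points is still a very large difference.

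The plan also says only that the method helps to secure unbiased results. That is softer than a guarantee, but the plan states no condition under which it would be true. None of these points supplies a reason to use LOCF as the sole method.

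**Conclusion.** The point holds. LOCF as the only rule for missing follow-up rests on an unstated assumption of no change after the last questionnaire, on an outcome the trial sets out to change. The assurance about bias is unsupported.

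Under the assumptions above, with 20% dropout per arm, the bias in the between-arm difference runs from −11.9 points (all losses early) through −6.0 (half early) to 0 (all late, stable practice), and to about +5 if practice wanes to an assumed 60%. Unequal early dropout, also assumed, enlarges the loss and can produce a difference where there is none. The direction is not fixed, so LOCF cannot be defended as conservative. For the group-by-time contrast it also claims more precision than the observed records support.

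The simulation ignores clustering. With four colleges the real uncertainty is larger, which is a separate matter.

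**What to change.** - Remove LOCF from the primary analysis and delete the sentence that claims accuracy and freedom from bias.
- Fit the planned GEE to all enrolled teachers in the arm to which their college was allocated, using every observed visit. Colleges are randomised and teachers are sampled and consented afterwards, so the analysis set should be described in those terms.
- Impute missing practice by multiple imputation under missing at random. Unweighted GEE on observed records alone needs a stronger assumption: that missingness is completely random or depends only on model covariates. Keep the imputation model small: arm, college, and baseline and month-1 practice. Each college lies in one arm, so college indicators already carry arm. At 85.6% practising, only about 0.144 × 57 = 8 intervention teachers would be non-practising, too few for a rich model.
- Report dropout by arm and visit.
- Add one sensitivity analysis that counts missing month-3 practice as non-practising. LOCF may stay only as a further sensitivity analysis.

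The cost is revised wording, a little more analysis work and somewhat wider intervals. Visits and data collection do not change. The sample size stays at 114, because it already allows for 20% attrition.
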